### Limitations

A limitation of this study could be a biased sample, as it is possible that only participants with a high level of interest and motivation will enroll in training courses. There could also be discontinuation of the study, as some participants might demonstrate poor performance results and may not want to participate anymore. To avoid this, the size of our initial sample will account for dropouts during the study. During the study (between the intervention and evaluations after 1 month and 1 year), participants may encounter a patient with anaphylactic shock in their clinical practice or attend training on the subject. This could affect their performance.

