### Statistical Analysis

#### Power Calculation

Sufficient sample size to detect a difference between the test and control groups in the score of the evaluation scale (primary outcome) using a 2-tailed independent *t* test was determined using power analysis. For α of .05 and 80% power to reject the null hypothesis of equal group means, when the population mean difference is 10 points (considered clinically relevant) and population SD of both groups is 20 points, a sample size of 128 (64 per group) is needed. The SD of 20 was used based on the results of a study on the use of case-based simulations with high-fidelity mannequins in teaching and retention of emergency management team skills [18]. In that study, the SD of the evaluation scores was <20 for all scenarios. To account for dropouts, we plan to recruit 150 participants.

For the secondary outcome (dichotomous version of the score of the evaluation scale), we performed power analysis using the planned sample size of 128 (64 per group). A chi-square test with α of .05 achieves 80% power to reject the null hypothesis of equal group proportions of successful assessments if the population difference between the group proportions is 21%-25%, where the proportion of successful assessments in the control group is assumed to be between 15% and 40%.

Sample size calculations were conducted using PASS 2019 Power Analysis and Sample Size Software [24].

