#### Statistical Methods

We will summarize categorical variables with frequencies and percentages, and we will summarize numerical variables with means and SDs or medians and IQRs in the case of asymmetric distributions. To highlight the differences between the groups at baseline, we will use the chi-squared test or Fisher exact test (if more than 20% of the expected frequencies are below 5) for categorical variables and independent samples *t* test or Mann-Whitney U test (in the case of asymmetric distributions) for numerical variables.

For the comparison of groups after 1 year (primary time point), we plan to use a *t* test for independent samples (or Mann-Whitney U test) for the evaluation scale score (primary outcome) and a chi-squared test (or Fisher exact test) for its dichotomous version (secondary outcome) and for the safety criteria. To compare groups at all time points (right after the intervention, after 1 month, and after 1 year) efficiently in one model, we will use appropriate mixed-effects regression models, which are able to appropriately take into account repeated measurements of the same patient. The power for detecting differences between groups with these models is even higher than with independent *t* tests or chi-square tests that were used in the power analysis.

To evaluate the short-term and long-term effectiveness of coping with stress, only the following dimensions will be included in the analysis: confrontation, distance, self-control, seeking social support, taking responsibility, escape/avoidance, planned problem solving, and positive reassessment. We will sum items to provide each of these scales. For each scale, groups will be compared using a linear mixed-effects regression model.

A *P* value <.05 will be considered as statistically significant.

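### Over-recruitment protects the number analysed but does not deal with performance-related dropout, and the 1-year test named uses none of the earlier scores that could

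*Protocol article*

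**What the plan says.** In Limitations, the protocol article names a dropout route tied to the outcome: "some participants might demonstrate poor performance results and may not want to participate anymore". The remedy follows directly: "To avoid this, the size of our initial sample will account for dropouts during the study".

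Power Calculation gives the numbers behind that remedy. "a sample size of 128 (64 per group) is needed", and then "To account for dropouts, we plan to recruit 150 participants". No dropout rate is stated.

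Procedures and Data Collection (Phase Two) schedules simulations at baseline, immediately after the intervention, at 1 month and at 1 year, and makes 1 year the primary time point. For that time point Statistical Methods names a *t* "test for independent samples (or Mann-Whitney U test) for the evaluation scale score (primary outcome"), with a chi-squared or Fisher test for the all-criteria and safety outcomes. The same section also plans mixed-effects models over the three post-intervention assessments. It presents them as an efficient joint comparison that allows for repeated measurements. They are not called the primary 1-year analysis, and baseline is not mentioned as part of them.

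**The concern.** On either reading of the Limitations sentence, the remedy does not fit the problem. If it means that discontinuation is avoided, enrolling more people does not change anyone's reason to leave. If it means that the consequences are avoided, a larger sample replaces lost numbers, not the particular people lost.

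A two-group test of 1-year scores needs a 1-year score from each person analysed and takes nothing from earlier visits. The article states no handling of missing 1-year scores, so as written the comparison rests on those who return. If low scorers leave and AR raises scores, more controls than AR participants fall in the range where leaving is likely. The control mean among returners is then raised more than the AR mean, and the estimated benefit is too small. The all-criteria and safety proportions at 1 year are compared in the same way and are open to the same selection.

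The trial collects the scores that would help. The Methodology part of the Discussion itself calls short-term performance a good predictor of later performance.

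**Working it through.** **1. The plan's own figures.** Inputs from Power Calculation: a two-sided test at the 5% level, power of 80%, a difference of 10 points and an SD of 20 points in each arm.

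- Normal approximation: n per arm = 2 × (1.960 + 0.842)² × 20² / 10² = 62.8, so 63.
- With the *t* distribution: 64 per arm, 128 in total, power 80.1%. The stated figure reproduces.
- Implied dropout allowance: (150 − 128)/150 = 22/150 = 14.7%.

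The arithmetic is right for its proper purpose, which is power.

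**2. What the 1-year comparison estimates among returners.** Suppose dropout depends on the 1-month score, which has correlation r with the 1-year score. Let m_T and m_C be the mean 1-month scores of returners in the test and control arms, in SD units from the full arm's own mean. Then

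expected completer difference = Δ + r × SD × (m_T − m_C).

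The number of participants does not appear in this expression.

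**3. Size, same mechanism in both arms.** From the document: Δ = 10, SD = 20, overall loss 14.7%. Assumed, because the document gives nothing: r from 0.5 to 0.7; log-odds of leaving falling by 1 or 2 per SD of the 1-month score, on the same scale in both arms; the 10-point effect already present at 1 month. The shifts r × SD × m come from numerical integration.

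| r | Slope | Loss control / test | Shift control | Shift test | Completer difference |
|---|---|---|---|---|---|
| 0.5 | 1 | 17.4% / 12.0% | +1.53 | +1.07 | 9.55 |
| 0.5 | 2 | 18.9% / 10.5% | +2.49 | +1.49 | 9.00 |
| 0.7 | 1 | 17.4% / 12.0% | +2.14 | +1.50 | 9.37 |
| 0.7 | 2 | 18.9% / 10.5% | +3.48 | +2.09 | 8.61 |

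Last row: 10 + 2.09 − 3.48 = 8.61. The bias is therefore about 0.5 to 1.4 points towards zero. It grows with heavier loss: at 30% overall and r = 0.7 the completer difference is about 9.0 (slope 1) or 7.9 (slope 2).

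**4. Sample size does not help.** Simulated trials with r = 0.6, slope 1 and about 21% / 15% loss gave a mean completer difference of 9.42 with 75 per arm and 9.39 with 300 per arm. An estimator using the earlier scores averaged 10.0 at both sizes.

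A closed form shows the same. Suppose the control arm loses its lowest 20% on the early score and the test arm its lowest 9.3%, with r = 0.5. The shift in each arm is r × SD × φ(z_p)/(1 − p):

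- control: 0.5 × 20 × 0.280/0.80 = 3.50
- test: 0.5 × 20 × 0.166/0.907 = 1.83
- bias: 1.83 − 3.50 = −1.67 at any sample size.

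**5. No true effect.** With the same mechanism in both arms, m_T = m_C and the bias is zero. Simulation agreed: 0.04 points and 4.9% rejections.

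**6. Mechanism differing by arm (hypothetical).** If performance drives dropout only among controls, with the step 3 assumptions, the completer difference is about 6.3 to 8.6 when the truth is 10, and about −1.5 to −3.6 when the truth is 0.

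**7. The model already planned.** In a simulation with r = 0.6, 75 per arm and 22% / 15% loss, the completer *t* test averaged 9.2. An estimate from post-intervention scores alone, close to the planned mixed model, averaged 10.0.

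**The case against.** The strongest reply is that the main remedy is already in the plan. A likelihood-based mixed model on the immediate, 1-month and 1-year scores handles dropout that depends on observed scores, which is the route the Limitations section describes. This stands. It narrows the point to which planned analysis is primary, whether baseline enters, and a wrong sentence about over-recruitment.

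The second reply is that analysis sets, imputation and sensitivity analyses for missing data usually belong in the analysis plan, which is not at hand. That also stands, so their absence from a condensed article is not the finding. The finding rests on a stated remedy that does not work and a stated 1-year test that is exposed.

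Several stronger readings are tempting and not supported:

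- *That the plan expects poor performers to leave.* The article says only that this could happen, and gives no rate.
- *That the 1-year estimate is biased in any event.* It is not if there is no true effect and the mechanism is the same in both arms.
- *That false positives are inflated.* This needs dropout that differs by arm at equal performance. The article suggests nothing of the kind: both arms have the same assessments and debriefing, and assessors are blinded.
- *That handling dropout properly would lift power from about 74% to about 94%.* Those are the simulated powers of the completer *t* test and of an analysis that uses all scores including baseline. But the *t* test with no dropout at all reaches only 86%, and using the post-intervention scores without baseline gives about 82%. Dropout handling is worth roughly 82 − 74 = 8 points. Most of the gap is the gain from baseline adjustment, a separate matter.

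**Conclusion.** The point holds in limited form and should be fixed. The Limitations sentence is wrong: 150 rather than 128 protects power against about 14.7% loss and does nothing about performance-related selection. The 1-year test named uses no earlier scores. If dropout follows earlier performance and AR works, that test understates the benefit by about 0.5 to 1.4 points of 10 at the loss the plan allows for, at any sample size. This is under half of the standard error of the difference with 64 per arm (20 × √(2/64) = 3.5), and it works against the intervention rather than for it.

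These sizes depend on an assumed correlation (0.5 to 0.7), an assumed dropout model and the same mechanism in both arms. Arm-specific dropout would give larger bias in a direction that depends on the arm, but the document offers no evidence of it.

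**What to change.** - In Statistical Methods, name the group contrast at 1 year from the already planned mixed-effects model as the primary analysis. Analyse all randomised participants in their assigned groups, with all three post-intervention scores as outcomes and the baseline score as covariate.
- Keep the *t* test (or Mann-Whitney U) at 1 year as a sensitivity analysis.
- In Limitations, say that recruiting 150 protects power against loss of up to about 15%, and that possible bias from performance-related dropout is addressed in the analysis.

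The cost is wording and slightly more modelling; no new data or participants are needed. The primary result would then rely on dropout being explained by observed scores (missing at random). A sensitivity analysis set out in the analysis plan can examine that assumption.

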### Conclusions

This will be the first study to evaluate the effectiveness of the use of AR in teaching medicine based on a clinical case of anaphylactic shock at the primary care level. With this study, we will evaluate the implementation of AR-related educational results in clinical practice. We will also be able to assess their long-term impact. This study will also serve as a basis for other research in the field of training with AR.

## Abbreviations

3D: 3-dimensional
ACLS: Advanced Cardiac Life Support
AR: augmented reality
RCT: randomized controlled trial
TALK: Target, Analysis, Learning Points, Key Actions
VR: virtual reality
WCQ: Ways of Coping Questionnaire
